### 3.13.2 Analyses of secondary objectives

1. For the "incidence of progression from pre-diabetes state to diabetes state", we will use Kaplan Meier methods to compare incidence between the two arms. The log-rank test will be used and Kaplan-Meier curves will be plotted for each treatment group.
2. Adverse events, including hospitalizations due to hypo- or hyperglycemia, morbidity. For adverse events outcomes, we must account for the possibility that participants may experience multiple episodes over the study period. Thus, we will use log-binomial models for repeated outcomes to examine the treatment effect on these outcomes
3. For costs outcomes, cost evaluation will be undertaken from the health program provider perspective. The health service use costs of the two strategies will be calculated at 12 months in both arms. Costs incurred between baseline and 12 months will be discounted at ??%. The mean cost of the two groups over 12 months will be compared using non-parametric tests. Results will be reported with 95% confidence intervals and uncertainty will be examined using sensitivity analysis. An incremental cost-effectiveness ratio will be calculated over the 12 months of the intervention. The need or otherwise for cost-effectiveness modeling will depend on there being economically important clinically significant differences in glycaemic control, as determined by the likely impact on and hence, long-term effects on morbidity and mortality. Whether any differences in glycaemic control are important will be informed by reviewing the cost-effectiveness of other interventions that have been evaluated using lifetime models. If such differences do exist, the modeling of the longer-term effects to assess the incremental cost per quality adjusted life-year will be conducted
4. For comparison of differences between the country sites, in regard to baseline context infrastructure situation for prevention and management of diabetes, these are baseline comparisons thus for continuous context variables, we will use the t-test statistic or the equivalent non-parametric test. For categorical context variables we will use the chi-square test statistic.
5. Similarly, for the degree of implementation of the intervention elements in each country, and differences between the country sites, we will compare the process evaluation variables/ indicators regarding ways in which program services and goods are provided (i.e. deviations) using the t-test statistic or the equivalent non-parametric test. For categorical context variables we will use the chi-square test statistic.
6. To compare changes in participant perceptions towards diabetes, physical activity, dietary behavior; and changes within contexts, as a result of implementing the intervention elements; we use multivariable linear regression mixed effects modeling with a random intercept, unstructured correlation matrix and robust standard errors, to evaluate changes over time in these outcomes of interest in relation to the assigned study arm. Visit month (categorical) at which the outcome is measured, study arm would be included in the model as fixed effects. The null hypothesis to be tested in this analysis would be that the mean changes at all the post-baseline visit months are equal between the treatment groups. The alternative hypothesis would be that the mean changes are not equal at, at least one post-baseline visit month.

We recognize that since sample size calculations for this trial were not based on the secondary outcomes, lack of significant differences in analysis of secondary outcomes might either be true lack of differences in these outcomes, or due to the fact that the trial was not sufficiently powered to detect differences in these outcomes. Thus interpretation of findings on secondary outcomes will be done with caution in case we do not detect any differences.

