## 3.8 Follow-up evaluations:

Each participant will be followed up to 12 months from the time of enrollment, or until his/her death or loss to follow-up. Active data collection will occur at baseline and months 3, 6 and 12. However participants with diabetes will return to their respective cluster health facilities monthly for their clinic visits and drug refills.

During follow-up study visits, we will conduct the following assessments:

1. Medical history assessment
2. Clinical evaluation of participants to assess any changes in clinical participants markers and outcomes
3. Physical measurements (weight, waist circumference and blood pressure),
4. Biochemical measurements including HbA1c and FPG (Uganda & South Africa only)
5. 7-day pedometer steps assessment
6. Participant diabetes knowledge
7. Illness perception
8. Social support and sources of support
9. Self-efficacy, autonomy support & self-regulation
10. Psychological adjustment
11. Quality of life & Stress
12. Diabetes treatment satisfaction
13. Adherence to study procedures and to intervention elements
14. Out of pocket expenditure and incremental cost on the system
15. Incremental cost to the health facility
16. Process evaluation

***Process Evaluation***: In any trial, a high degree of compliance to the intervention elements is necessary to minimize decrease in statistical power and obtain unbiased results. In the case of non-compliance that is associated with both intervention element(s) and the study outcomes of interest, there is a particularly serious threat to validity. However, the best method for ensuring full compliance is to monitor compliance with the trial processes. Thus, participants will receive encouragement at their monthly visits to take their medications at the same time every day, and identify a Care Companion to provide medication reminders, as well as healthy lifestyle adherence. Research nurses will assess compliance in three ways: direct questioning and pill count assessed at each monthly visit, and biochemical assessment of plasma glucose. Research nurses will also make an effort to identify and address barriers to compliance.

Table 15 summarizes the schedule of study procedures and tools to be applied.

Table 15: Schedule of study procedures

| **Study Activity** | | **-7 to 0 days** | **BASELINE** | **M3** | **M6** | **M12** |
| --- | --- | --- | --- | --- | --- | --- |
| **I. Consent forms** | Screening consent | X |  |  |  |  |

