## 3.9 Outcomes of interest:

*Primary outcomes of interest*

Among participants with pre-diabetes, the primary outcome of interest will be reduction in plasma glucose between baseline and month 12 of follow-up. We hypothesize that participants with pre-diabetes in the facility + community arm will on average have a higher reduction in their HbA1c reading by the end of follow-up compared to participants with pre-diabetes in the facility alone arm, and the current practice arm in Uganda.

Regarding participants with type 2 diabetes, research has shown that, reduction of HbA1c level by 1% among such individuals leads to: a) 19% less likelihood of cataracts, b) 16% less likelihood of heart failure, and c) 43% less likelihood of amputations or death due to peripheral vascular disease [Anon 1993]. Further the UK Prospective Diabetes Study (UKPDS) [King et al 1999], and the Diabetes Control and Complications Trial (DCCT) demonstrated that improving HbA1c by 1% for people with type 1 diabetes *or* type 2 diabetes cuts the risk of microvascular complications by 25%. Therefore among participants with diabetes, the primary outcome of interest will also be reduction of their plasma glucoce levels. A participant will be classified as having had their plasma glucose reduced if:

1. Their HbA1c reading at month 12 is reduced to below 53 mmol/mol, or
2. Their HbA1c reading at month 12 is 5 mmol/mol below their baseline reading.

*Secondary outcomes of interest*

Secondary outcomes in this trial will include:

a) Incidence of diabetes among participants with pre-diabetes

b) Incidence of conversion from a state of pre-diabetes to normal plasma glucose levels.

c) Incidence of adverse events, including hospitalizations due to hypo- or hyperglycemia, or complications of diabetes.

d) Behavioral outcomes, including diet, physical activity, foot care, tobacco and alcohol consumption.

e) Costs of implementation of the intervention elements

f) Participant satisfaction with the individual intervention elements, including self-management

g) Differences between the country sites, in regard to baseline context infrastructure for prevention and management of T2D

h) Degree of implementation of intervention elements in each country, and differences between country sites informed by site-specific process evaluations

i) Effect of the interventions on perceptions towards diabetes, life style measures including physical activity, dietary behavior, etc.

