Further, we project a loss to follow-up of up to 10% over the 12 months follow up, thus the sample sizes obtained were accordingly adjusted upwards by 10%. Table 16 (a) provides a summary of the estimates used, and the sample size estimates obtained.

Table 16 (a): Parameter value estimates used in sample size calculations for participants with pre-diabetes

| **Parameter** | **Estimate** | | |
| --- | --- | --- | --- |
| Level of significance (α) | 5% | | |
| Power (1-β) | 80% | | |
| Primary outcome of interest | Mean change in HbA1c reading | | |
| Standard deviation (σ), of mean change in HbA1c | 2.5 | | |
| Minimum anticipated difference between arms, in primary outcome by month 12 | $\left( \mu_{0}-\mu_{1} \right)$ =  5 mmol/mol | | |
| Required sample size per arm, before adjusting for clustering (*n_i_*) | 34 | | |
|  | Uganda | South Africa | Sweden |
| Number of clusters | 9 | 2 | 4 |
| Inter-cluster correlation (ρ) | 0.200 | 0.044 | 0.070 |
| Sample size per arm, after adjusting for clustering (n) | 112 | 129 | 158 |
| Sample size per arm, after further adjusting for estimated loss to follow-up of 10% | 124 | 142 | 174* |

* *For Sweden, at least 87 participants with pre-diabetes will need to be immigrants of non-European origin, and at least 87 participants with pre-diabetes will need to be immigrants of European origin*

*Sample size for participants with diabetes*

A prospective cohort study among patients with diabetes in the United Kingdom showed that people with type 2 diabetes who reduce their HbA1c level by 1% are: a) 19% less likely to suffer cataracts, b) 16% less likely to suffer heart failure, and c) 43% less likely to suffer amputation or death due to peripheral vascular disease [Stratton et al. 2000]. Therefore among participants with diabetes, we aim at reducing their plasma glucose levels by month 12. A participant with diabetes will be defined as having had their plasma glucose reduced if:

1. Their HbA1c reading at month 12 is reduce to below 53 mmol/mol, or
2. Their HbA1c reading at month 12 is 5 mmol/mol below their baseline reading.

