**Table 3: Details of tools, sources and data collection points for Part III**

| Questionnaires | Source | BL | M2-11 | EL |
| --- | --- | --- | --- | --- |
| **Out of pocket expenditure: Individual and family questionnaire** | Prepared by [name] | X |  | X |
| **Health facility survey – to be administered to head of health facility*** | Prepared by [name] |  | X |  |
| **EPOCH – to be conducted by researcher and collected one per community*** | Environmental Profile of a Community’s Health (Clara Chow – Population Health Research Institute, Hamilton) |  | X |  |

* Not included in this set of data collection tools

| **SECTION 21: Out of Pocket Expenditure related to type 2 diabetes** | | | |
| --- | --- | --- | --- |
| **SECTION 21A: Out of Pocket Expenditure – Outpatient cost** | | | |
| **S.NO:** | **Questions** | **Response** | **Code** |
| A | Do you usually spend any money on medication and other related costs? | 1 Yes regularly  2 Yes occasionally  0 No  **If NO, SKIP to B** | OOPO_1a |
|  | **In the last month, how much did you spend on the following items in relation to treatment of type 2 diabetes?**  *Please record in respective local currency for each setting: Ug Sh (Uganda)/SAR (South Africa)/SEK (Sweden)* | | |
| B | Medicine:  1. Diabetes medication  2. Other medication | 1. └─┴─┴─┴─┴─┴─┴─┘  2. └─┴─┴─┴─┴─┴─┴─┘ | OOPO_1b1  OOPO_1b2 |
| C | Consultation fees  Not applicable = 888 | └─┴─┴─┴─┴─┴─┴─┘  └──┴──┘ | OOPO_1c |
| D | Laboratory tests  Not applicable = 888 | └─┴─┴─┴─┴─┴─┴─┘  └──┴──┘ | OOPO_1d |
| E | Other supplies  Not applicable = 888 | └─┴─┴─┴─┴─┴─┴─┘  └──┴──┘ | OOPO_1e |
| F | Food while at the health facility  Not applicable = 888 | └─┴─┴─┴─┴─┴─┴─┘  └──┴──┘ | OOPO_1f |
| G | Appreciation of health worker  Not applicable = 888 | └─┴─┴─┴─┴─┴─┴─┘  └──┴──┘ | OOPO_1g |
| H | Transport ( to and from facility)  Not applicable = 888 | └──┴──┘ |  |

O

| **SECTION 21B: Out of Pocket Expenditure – Hospitalisation cost** | | | | | |
| --- | --- | --- | --- | --- | --- |
| I | In the past 12 months, how many times were you hospitalized ? | Number of times └─┴**─┘**  **If 0 SKIP to SECTION 21C** | | | OOPI_1i |
| **For each hospitalization** (max 3 – if more, take last 3) can you answer the following questions | | | | | inst_oopi1 |
|  |  | **1** | **2** | **3** |  |

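### The adverse-event analysis is meant to handle several episodes per person, but the log-binomial model it names counts repeats within one record once and has no person-time term

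*Protocol*

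**What the plan says.** Section 3.9, secondary outcome (c), is "Incidence of adverse events, including hospitalizations due to hypo- or hyperglycemia, or complications of diabetes".

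Section 3.13.2, item 2, gives the analysis. It states that "we must account for the possibility that participants may experience multiple episodes over the study period" and draws the model from that: "Thus, we will use log-binomial models for repeated outcomes to examine the treatment effect on these outcomes". It does not say whether one repeated outcome is a study visit, a month or some other period, and it names no follow-up-time term.

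On timing, section 3.8 says: "Active data collection will occur at baseline and months 3, 6 and 12". It adds that "participants with diabetes will return to their respective cluster health facilities monthly for their clinic visits and drug refills", and that "Each participant will be followed up to 12 months from the time of enrollment, or until his/her death or loss to follow-up". Section 3.10 adds that "we project a loss to follow-up of up to 10% over the 12 months follow up".

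Section 21B of the data collection tools asks for a count: "In the past 12 months, how many times were you hospitalized". It takes details of at most the last three stays and has no field for their dates. Participants with pre-diabetes finish the interview before reaching it.

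**The concern.** The reason given and the model chosen do not fit well. If multiple episodes must be accounted for, the natural response variable is the number of episodes over the time observed. A log-binomial model has a 0/1 response. Used for repeated outcomes, it lets a person contribute an event in several records, but a second or third episode inside one record adds nothing.

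Time at risk raises a related issue. The three gaps between study visits are 3, 3 and 6 months long, and some people leave or die part-way through one. A model of risk per record, with no person-time term, mixes 3-month and 6-month risks and treats a partly observed record like a full one.

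This is the only adverse-event analysis the protocol describes. If episodes recur within people, the arm comparison would understate a difference in episode rates, and the repeat hospitalisations that give the outcome its weight would be only partly counted.

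**Working it through.** **Is there a figure to reproduce?** No. The protocol gives no event rate, effect size or power for adverse events, so the size of the problem can only be shown over assumed ranges.

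**Inputs from the protocol.** Log-binomial model for repeated outcomes (3.13.2, item 2). Study visits at months 3, 6 and 12, so possible records of 0.25, 0.25 and 0.5 years. Monthly clinic contact for participants with diabetes. Follow-up of up to 12 months (3.8). Loss of up to 10% (3.10).

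**Assumptions.** True rate ratio 2/3. Control-arm rate 0.1 to 1.2 episodes per person-year. Between-person frailty variance θ from 0 (none) to 4 (strong recurrence in the same people).

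**Formulae.** For a record with expected count μ = rate × length:

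- P(at least one) = 1 − exp(−μ) if θ = 0, otherwise 1 − (1 + θμ)^(−1/θ)
- ratio shown = ΣP(intervention) / ΣP(control)
- share of control-arm episodes not counted = 1 − ΣP(control) / Σμ(control)

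**Worked case: 0.6 v 0.4 per year, 3/3/6-month records.**

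- θ = 0, control: μ = 0.15, 0.15, 0.30; P = 0.1393, 0.1393, 0.2592; sum 0.538. Not counted: 1 − 0.538/0.6 = 10%.
- θ = 0, intervention: μ = 0.10, 0.10, 0.20; P = 0.0952, 0.0952, 0.1813; sum 0.372. Ratio 0.372/0.538 = 0.69.
- θ = 4: control sum 0.401 (33% not counted), intervention sum 0.298. Ratio 0.298/0.401 = 0.74.

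**Ratio shown when the true rate ratio is 0.67 (range: θ = 0 to 4).**

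| Control rate per year | Monthly records | 3/3/6-month records | One 12-month record | Not counted, 3/3/6 |
| --- | --- | --- | --- | --- |
| 0.1 | 0.67 | 0.67-0.69 | 0.68-0.71 | 2-8% |
| 0.3 | 0.67-0.68 | 0.68-0.71 | 0.70-0.76 | 5-21% |
| 0.6 | 0.67-0.69 | 0.69-0.74 | 0.73-0.81 | 10-33% |
| 1.2 | 0.68-0.71 | 0.71-0.78 | 0.79-0.85 | 19-48% |

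**Effect on power.** A simulation used 265 per arm (the Ugandan arm size), a true rate ratio of 0.6, 3/3/6-month records and no clustering by facility. Power for counts against yes/no records was 0.34 v 0.34 at 0.1 per year (θ = 0), 0.30 v 0.29 at 0.1 per year (θ = 3), 0.72 v 0.68 at 0.3 per year (θ = 1) and 0.82 v 0.69 at 1.0 per year (θ = 3).

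**Unequal loss, if data were collapsed to ever/never.** Take a true ratio of 0.70, 0.2 v 0.14 per year, θ = 0, and assume people lost are seen for half a year on average.

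- Control with 10% loss: 0.9 × 0.1813 + 0.1 × 0.0952 = 0.1727.
- Intervention with no loss: 0.1306. Ratio 0.1306/0.1727 = 0.76.
- Intervention also with 10% loss: 0.9 × 0.1306 + 0.1 × 0.0676 = 0.1243. Ratio 0.1243/0.1727 = 0.72.

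**The case against.** A reader might infer that repeat episodes and follow-up time are simply thrown away and that the arm effect is bound to be diluted. The documents do not support that. The model is specified for repeated outcomes, so an event in each of several records is kept, and only repeats inside one record are lost. Someone lost to follow-up stops contributing records, so only exposure within a part-completed record goes unhandled. One yes/no per study visit is itself an inference, because the unit is undefined and participants with diabetes are seen monthly. With monthly records the ratio stays at or below 0.69 for rates up to 0.6 per year.

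Other points also carry weight. A risk ratio per record is a legitimate estimand, and its lying nearer 1 than a rate ratio is not bias in itself. In the same outcome list, incidence is also used for changes of state, so it need not mean episodes per unit time. Visit terms or an offset could be set out in an analysis plan not shown here. Eligibility points towards low rates: diabetes diagnosed no more than 12 months earlier or pre-diabetes, prior heart disease or stroke screened out in the tools' eligibility check, and 124 of 265 participants per Ugandan arm with pre-diabetes. The outcome is secondary, and section 3.13.2 promises cautious reading of null secondary results.

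These arguments limit the size of the problem but do not remove it. The protocol does more than leave a detail open: it names a model and justifies it by a feature of the data which that model handles only in part.

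**Conclusion.** The point holds in a limited form. The log-binomial model serves its stated purpose poorly: it counts episodes in the same record once and has no stated person-time term, while record lengths and follow-up differ and the repeated unit is undefined.

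The consequence depends on event rates the protocol does not give. It is negligible if events are rare or records are monthly. It is material only if events are frequent or strongly clustered within people, or if data are collapsed to one 12-month record. The figures rest on a true rate ratio of 0.67, frailty variance of 0 to 4 and full follow-up, except in the loss example. Since the outcome is secondary with no planned power, severity is minor to moderate.

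**What to change.** In section 3.13.2, item 2, replace the log-binomial model with negative binomial regression on the number of episodes per participant, or Poisson regression with cluster-robust, small-sample-corrected standard errors. The correction is needed because there are only 9 + 2 + 4 = 15 clusters. Use log follow-up time as offset, arm and country as fixed effects, and facility as the cluster. Report the rate ratio and the rate difference, and keep the proportion with at least one event as a descriptive line. If a risk ratio is preferred, define the record and justify that estimand.

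The change of wording is short, but the data need checking. Episode counts and time under observation must be available for every participant, including those with pre-diabetes, who do not reach the hospitalisation form shown. That form gives a 12-month count without dates and the reason for at most three stays, so attributing stays to hypo- or hyperglycaemia or to complications may need another source or a small addition to the follow-up form.

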## 2.2 Specific objectives

### 2.2.1 Primary objectives

The primary objectives of the trial are as follows:

1. To determine the combined effect of the facility+ community strategies, in controlling blood sugar levels among patients with T2D
2. To determine the effect of the facility+ community strategies, in reducing blood sugar levels among individuals with pre-diabetes
3. To determine the effect of the facility+ community strategies, on retention into care among patients with T2D.
4. To estimate the incremental provider cost per patient of managing patients with T2D, as a result of implementing the facility+ community strategies.
5. To estimate the incremental client cost per patient of managing patients with T2D, as a result of implementing the facility+ community strategies.

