Thus we will aim at maximizing the proportion of participants with diabetes whose blood sugar levels has been reduced, per the criteria defined above. We aim at being able to detect a difference of at least 2% in the percentage of participants with diabetes with reduced plasma glucose levels by month 12 between the trial arms (effect size). The required sample size before adjusting for clustering, at 80% power and 5% level of significance is 58 participants per arm. We have also assumed that in the intervention arm we shall attain reduction in plasma glucose per the criteria given above, in 30% of participants with diabetes (P_1_= 0.3). For this first stage calculations, we used the formula as described in Hayes and Bennett (1999) [Hayes 1999] for proportions, that is:

[figure not shown]

where: $n_{i}$ = initial sample size (58)

$P_{0}$ = Proportion of participants with diabetes in the comparison (control) arm, whose plasma glucose levels are controlled by month 12 (32%)

$P_{1}$ = Proportion of participants with diabetes in an intervention arm, whose plasma glucose levels are controlled by month 12 (30%)

For an estimate of inter-cluster correlation (ICC) among individuals with diabetes, we found only two publications of cluster randomized trials reporting ICC estimates among diabetes patients, one by Littenberg et al (2006) in which they report an inter-cluster correlation (ICC) coefficient for HbA1c among patients with diabetes of 0.055 [Littenberg et al. 2006]; and another by Singh et al (2015) in which they report an ICC coefficient of 0.091 [Singh et al. 2015]. We use some of these estimates. For Uganda we used an ICC value of 0.0.091 to obtain a sample size of 128 participants, for South Africa we used an ICC value of 0.020 to obtain a sample size of 136, whereas for Sweden we also used an ICC value of 0.020 to obtain a sample size of 81; all per study arm.

Once again for Sweden, there will be a further interest to compare the primary outcome of interest between immigrant participants of non-European origin versus immigrant participants of European origin. In order to allow for this sub-analysis, the sample size of 81 for Sweden was doubled to 162 to enable detection of the same effect size immigrant participants of non-European origin versus immigrant participants of European origin.

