Similarly, we project a loss to follow-up of up to 10% over the 12 months follow up, thus the sample sizes obtained were accordingly adjusted upwards by 10%. Table 16 (b) provides a summary of the estimates used, and the sample size estimates obtained.

Table 16 (b): Parameter value estimates used in sample size calculations for participants with diabetes

| **Parameter** | **Participants with Diabetics** | | |
| --- | --- | --- | --- |
| Level of significance (α) | 5% | | |
| Power (1-β) | 80% | | |
| Primary outcome of interest | % of participants with reduced plasma glucose | | |
| Proportion of participants with reduced HbA1c by month 12 in control arm ($P_{0}$) | 30% | | |
| Minimum anticipated difference between arms, in primary outcome by month 12 | $\left( P_{0}-P_{1} \right)$ = 2% | | |
| Required sample size per arm, before adjusting for clustering (*n_i_*) | 58 | | |
|  | Uganda | South Africa | Sweden |
| Number of clusters | 9 | 2 | 4 |
| Inter-cluster correlation ($\rho$) | 0.091 | 0.020 | 0.020 |
| Sample size per arm, after adjusting for clustering (n) | 128 | 136 | 81 |
| Sample size per arm, after further adjusting for estimated loss to follow-up of 10% | 141 | 150 | 90 |

* *For Sweden, at least 90 participants with diabetes will need to be immigrants of non-European origin, and at least 90 participants with diabetes will need to be immigrants of European origin*

Figure 15 summarizes the trial and the sample sizes to be used at each site per study arm.

Figure 15: Schema for the trial

^ф^265 = 124 with pre-diabetes, & 141 with diabetes

^€^292 = 142 with pre-diabetes, & 150 with diabetes

^¥^353 = 174 with pre-diabetes (87 immigrants of European origin plus 87 immigrants of non-European origin),

& 179 with diabetes (90 immigrants of European origin plus 90 immigrants of non-European origin)

Overall total participants

N=1997

Uganda

n=795

South Africa

n=584

Sweden

n=706

Follow-up

Month 3

Month 6

Month 12

Baseline evaluation

Facility only

n=292^€^

Facility+ community

n=292

Facility only

n=353^¥^

Facility+ community

n=353

Facility only

n=265^ф^

Facility+ community

n=265

Control

n=265

Randomization

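### Mean 12-month cost is to be compared by non-parametric tests; read as rank tests, these do not test mean cost, so the p-value can disagree with the incremental cost reported beside it

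*Protocol*

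**What the plan says.** Two of the primary objectives in Protocol section 2.2.1 concern cost: "To estimate the incremental provider cost per patient of managing patients with T2D" (objective 4) and "To estimate the incremental client cost per patient of managing patients with T2D" (objective 5). Section 3.9 also lists implementation cost among the secondary outcomes.

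The analysis is in section 3.13.2, item 3, which takes the provider perspective. It says: "The mean cost of the two groups over 12 months will be compared using non-parametric tests". It adds: "Results will be reported with 95% confidence intervals and uncertainty will be examined using sensitivity analysis", and then: "An incremental cost-effectiveness ratio will be calculated over the 12 months of the intervention". It names no test and does not say how the interval will be obtained.

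Item 4 of the same section, on continuous context variables, says "we will use the t-test statistic or the equivalent non-parametric test". Item 5 repeats that pairing for process indicators.

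**The concern.** The quantity named is a mean, and a mean is what the cost objectives need. Mean cost per patient multiplied by the number of patients gives the budget, and the ratio divides a difference in mean cost by a difference in effect. The usual non-parametric counterpart of the t-test, the Mann-Whitney test, addresses something else: whether a patient drawn from one arm tends to cost more than a patient drawn from the other. The two questions coincide when one cost distribution is simply a shifted copy of the other. They can separate when most patients cost slightly more and a few avoid a very large cost.

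That pattern is plausible here. The community component adds recurring activity (peer groups, link teams, mentoring) for the patients in that arm, and hospitalisations are a listed outcome whose costs are collected separately. At stake is a report in which the cost p-value points one way and the incremental cost, its interval and the ratio point another.

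**Working it through.** **No figure to reproduce.** The protocol states no cost mean, standard deviation, hospitalisation rate or power for the cost comparison.

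**Inputs from the protocol.**
- Significance level 5%, taken as two-sided because the sample-size formula uses Z at α/2 (section 3.10: "at 80% power and 5% level of significance is 58 participants per arm").
- Patients with diabetes per arm before allowance for loss (Table 16(b)): "Sample size per arm, after adjusting for clustering (n) | 128 | 136 | 81" for Uganda, South Africa and Sweden. Check with the protocol's fixed-cluster formula, n·k·(1−ρ)/(k−n·ρ), for Uganda: 58 × 9 × 0.909 / (9 − 58 × 0.091) = 474.5 / 3.722 = 127.5, rounded up to 128.

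**What each method tests.** For costs X (control) and Y (intervention):
- Comparison of means: E(Y) − E(X) = 0.
- Mann-Whitney: the null is identical distributions, and the test responds to P(Y > X) + ½P(Y = X) differing from ½.

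**Assumed cost model (not from the protocol).** Routine cost is gamma with mean 100 and SD 50. Hospitalisation occurs with probability p and adds a gamma cost with mean h. The intervention arm has a fixed addition a. Mean cost = 100 + a + p·h. Patients are independent, and the tests are a two-sided 5% Mann-Whitney and a Welch t-test.

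*Equal means, h = 500.* The control mean is 100 + 0.10 × 500 = 150.

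| a | p, intervention | Intervention mean | Rank test rejects, 128 per arm |
|---|---|---|---|
| 5 | 9% | 105 + 45 = 150 | 8–10% |
| 10 | 8% | 110 + 40 = 150 | 23% |
| 15 | 7% | 115 + 35 = 150 | 43–45% |
| 25 | 5% | 125 + 25 = 150 | 83–86% |

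The comparison of means rejects in about 5% throughout. Ranges are from repeated simulation runs.

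*Opposite directions, h = 1,500, a = 25, hospitalisation 10% v 5%.* Means are 100 + 150 = 250 and 125 + 75 = 200, a saving of 50. The rank test is significant in 83–84% of trials at 128 per arm, driven by the higher routine cost.

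*A real increase missed, h = 1,000, a = 0, hospitalisation 5% v 15%.* Means are 150 and 250. At 128 per arm the rank test detects this in 25–28% of trials and the comparison of means in 53–56%.

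**Second set of assumptions, 4,000 trials per scenario, 128 per arm.**
- Log-normal costs, both means 100, log-SD 1.0 v 0.6: rank test 85%, Welch 6%.
- Routine cost 100 v 120, hospitalisation 10% v 7.5% at 800, so 100 + 80 = 120 + 60 = 180: rank test 87%, Welch 5%.
- Equal medians of 100, log-SD 0.6 v 1.0, means about 120 v 165: rank test 6%, Welch 65%.
- Identical distributions: both about 5%.

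The mismatch appears in both directions under both sets of assumptions and is absent when the distributions are identical.

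**The case against.** **The rank test is inferred.** Item 3 names no test, and a bootstrap or permutation test of the mean difference is also non-parametric. The supporting usage is in items 4 and 5, which concern context and process variables. This stands as an ambiguity. It does not remove the point, because item 3 speaks of tests, never mentions resampling, and sits in a section that uses the term for the alternative to the t-test. If a bootstrap was meant, the sentence still needs to say so.

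**The objectives are to estimate.** An estimate with the promised 95% interval answers objectives 4 and 5 without a p-value, cost is also listed as a secondary outcome, and it plays no part in the sample-size hypothesis. This stands. A reader might infer that the cost estimate or the cost-effectiveness ratio would be wrong. The documents do not support that, since neither is computed from the test.

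**The size depends on chosen inputs.** This stands. The highest rejection rates come from the largest offsets. Facility care is common to the two main arms, so only the community component adds cost between them; Uganda's current-practice arm is the exception.

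**Independent patients are assumed in a cluster trial.** This stands too. With three clusters per arm and an assumed cost intracluster correlation of 0.02 to 0.09, an unadjusted Welch test itself rejects in 17–39% of trials with no arm difference. The 5% for means describes the comparison without clustering and does not forecast this trial's error rate.

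**Conclusion.** The sentence pairs mean cost with a class of tests that, on the reading most consistent with the section, does not test mean cost. The consequence is confined to the p-value, which may contradict the incremental cost, its interval and the ratio. Item 3 is written from the provider perspective, so it bears directly on objective 4; it bears on objective 5 if the same method is carried over to client cost.

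Under assumed costs, independent patients and equal means at 128 per arm, the rank test rejects in roughly 10% to 85% of trials, against about 5% for means. These figures show that the conflict can be large. They do not show that it will be large here, because the protocol gives no cost distribution, and under a pure shift the conflict disappears. A reader might also infer that a primary hypothesis test is invalid; the cost objectives are estimation objectives, and the HbA1c analyses are untouched. This is a wording correction worth making before analysis.

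**What to change.** Replace the sentence in item 3 with:

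> The difference in arithmetic mean cost per patient between arms will be estimated with a 95% confidence interval from a regression model for mean cost (for example a GLM or GEE adjusted for site, with allowance for clustering and a small-sample correction). Rank tests will not be used for the cost comparison, and the same mean difference will be used in the incremental cost-effectiveness ratio.

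Do not bootstrap the randomised units within site. Section 3.10 gives South Africa two clusters, hence one per arm, so resampling clusters there yields an interval of zero width. Uganda has nine clusters over three arms, about three per arm, and a percentile cluster bootstrap with three per arm rejected in about 18–22% of simulated trials with no difference. If a patient-level bootstrap is used, state that it does not capture between-cluster variation. With one cluster per arm, no model can separate arm from cluster within South Africa alone, so a site-specific interval there needs the same caveat.

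The cost is a change of analysis wording, with no change to data collection. The downside is wider intervals when costs are very skewed.
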